### Participants

#### Recruitment

Recruitment for this trial began in March 2021 and ran for 12 months. Participants will be recruited from the community (*via* advertisements on social media, research participant recruitment websites, and university-managed webpages), and from the South London and Maudsley outpatient ED service.

People interested in the study will receive verbal and written information about the study rationale, aims, and methodology. Specifically, participants are told that there is tentative evidence to suggest both tDCS and ABMT may reduce craving for food and episodes of loss of control eating, and that the present study will be the first to examine whether combining these two interventions may alleviate symptoms of BED. After providing written consent, participants will be screened against inclusion and exclusion criteria.

#### Inclusion criteria

Participants eligible for the trial must comply with all of the following criteria at randomization:
Aged 18–70 years.Right handedOverweight or obese (body mass index (BMI) ≥25 kg/m^2^).Meet diagnostic criteria for full-syndrome BED diagnosis according to the Diagnostic and Statistical Manual 5^th^ Edition (2013).Normal or corrected to normal vision.Access to a laptop or desktop computer with a webcam.

#### Exclusion criteria

Insufficient knowledge of the English language.Pregnancy or suspected pregnancy.Current significant or unstable medical or psychiatric disorder needing acute treatment in its own right.A lifetime diagnosis of substance dependence, psychosis, bipolar disorder, or borderline personality disorder.Developmental or neurological disorder (e.g., dementia, attention deficit hyperactivity disorder, autism spectrum disorder).Psychotropic medication other than a stable dosage of an antidepressant (e.g., selective serotonin reuptake inhibitor) for at least 14 days prior to study enrolment.Non-removable metal parts in the area of the head (excluding dental work).History of epilepsy or migraine.Use of a pacemaker.

We will report the number of participants excluded, with reasons, and the number who decline consent or withdraw from the study, with reasons where provided.

### Sample size

As TANDEM aims to establish feasibility rather than between-group differences, an a priori sample size calculation is not necessary. Guidance suggests that, where available, sample size should be based on previous feasibility or pilot studies of a similar intervention, or with a similar primary outcome measure or trial design. Where this information is lacking, it is argued that a total sample between *n* = 12 and *n* = 50 is sufficient for robust assessment of feasibility outcomes (39). Previous comparable trials in BED included 20 participants in each trial arm [e.g., (31, 41)]. As this trial includes four arms, we have chosen a target end study sample size of *n* = 80. Assuming the attrition to follow-up rate is ~10% [as found in previous recent BED treatment trials, e.g., (42)], we will recruit an actual sample size of 88 (22 participants/group).

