**Methods:**

This protocol describes a feasibility single-blind randomized sham-controlled trial of concurrent self-administered tDCS and ABMT in adults with BED (The TANDEM Trial). Eighty adults with BED will be randomly assigned to one of four groups: ABMT with real or sham self-administered tDCS, ABMT only, or waiting list control. In the treatment arms, participants will complete 10-sessions of their allocated intervention over 2–3 weeks. Outcomes will be assessed at baseline (T0), immediately post treatment (T1), and 6 weeks after end of treatment (T2), and at comparable timepoints for participants in the waitlist control group. Feasibility will be evaluated by assessing recruitment/retention rates and blinding success. Acceptability will be assessed quantitatively *via* participant ratings and qualitatively *via* semi-structured interviews. Episodes of binge eating at follow-up will be the primary clinical outcome and rate ratios from Poisson regression will be reported. Secondary outcomes will assess changes in ED and general psychopathology, attention bias toward high calorie foods, and executive function.

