Two studies have examined the effect of multiple sessions of tDCS on BED symptoms. A randomized sham-controlled trial involving 32 adults examined the effect of 10 sessions of tDCS on attention bias toward food, craving for food, and cognitive flexibility (31). In this trial, tDCS was given with the anode over the left dlPFC and the cathode over the right dlPFC (2mA/20 min). Sessions were 3/week until 10 sessions had been completed. At post-treatment and 45 day follow up, real tDCS treatment was associated with a greater reduction in attention bias toward food, a greater reduction in craving for food, and an improvement in cognitive flexibility. However, effect sizes were small, and the authors acknowledged several study limitations, including a small sample (*n* = 32) and concerns about the effect of poor eye-tracker calibration on the reliability of attention bias outcomes.

Our group has also recently completed an RCT of six sessions of right-anodal tDCS targeting the dlPFC delivered over 3 weeks in adults with BED [*n* = 65, (32) for protocol]. In this trial, we examined whether symptoms of BED were improved by an intervention involving the concurrent delivery of tDCS and approach bias modification training, a form of CBM which targets approach bias toward high-calorie foods. Participants were randomly allocated to one of three study groups (approach bias modification training with real tDCS, approach bias modification training with sham tDCS, or wait-list control) and outcomes were assessed at baseline, 3-weeks post-randomization, and 7-weeks post randomization. Clinical and neurocognitive outcomes are yet to be published; however, findings from a qualitative study of the treatment experience indicate that this combined approach to treatment is tolerable and acceptable (33).

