### Randomization

The study will use a randomized controlled design, stratified by age, gender and BMI. Participants will be randomly allocated to a study group in a 1:1:1:1 ratio. Randomization will be completed using the Sealed Envelope Simple+ randomization service (https://www.sealedenvelope.com/). After completing the T2 assessment, participants in the waiting control arm will be offered ABMT.

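### The planned sample size is stated in two ways: 80 randomised in the abstract, but 88 recruited to leave 80 at the end in the Sample size section; one of the two trials cited for 20 per arm had only 32 participants

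*Protocol article*

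**What the plan says.** The Methods paragraph of the abstract gives the number entering the trial: "Eighty adults with BED will be randomly assigned to one of four groups".

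The Sample size section declines a formal calculation because the trial is about feasibility. It sets the arm size by precedent: "Previous comparable trials in BED included 20 participants in each trial arm [e.g., (31, 41")]. With four arms this leads to the statement that "we have chosen a target end study sample size of *n* = 80". The section then allows for loss, "Assuming the attrition to follow-up rate is ~10"%, and concludes "we will recruit an actual sample size of 88 (22 participants/group").

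The Randomization section adds "Participants will be randomly allocated to a study group in a 1:1:1:1 ratio".

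The Introduction describes reference 31 in these terms: "A randomized sham-controlled trial involving 32 adults examined the effect of 10 sessions of tDCS". Later in the same paragraph it gives the sample of 32 as one of that study's limitations.

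**The concern.** The number 80 has two meanings. In the abstract it counts people at randomisation. In the Sample size section it counts people at the end of follow-up, and the number entering is 88. A reader cannot tell from the article how many participants the trial planned to randomise.

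This matters a little more here than in most trials, because recruitment and retention are among the feasibility results, meant to show what a larger trial would need in time and resources. Recruitment is naturally set against the planned number. The Trial progress section says recruitment has already ended, so with two published figures the comparison could be chosen after the count is known.

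The second inconsistency concerns the basis for 20 per arm. As there is no formal calculation, the cited precedents are the only stated reason for that arm size, and one of them does not fit the article's own description of it.

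**Working it through.** **Inputs**

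- Number randomised according to the abstract: 80.
- End-of-study target (Sample size): 80, that is 20 in each of four arms.
- Attrition to follow-up (Sample size): about 10%.
- Number to recruit (Sample size): 88, or 22 per group.
- Allocation (Randomization): equal across four arms.
- Size of the reference 31 trial (Introduction): 32 in total, randomised and sham-controlled. Its allocation ratio is not given.
- Size of the reference 41 trial: not given in the article.

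**1. Reproducing the plan's own figure**

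Multiplying the target by one plus the loss rate gives 80 × 1.10 = 88 in total and 20 × 1.10 = 22 per arm, exactly as stated.

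Dividing by the proportion retained gives 80 / 0.90 = 88.9, or 89, a difference of one participant. In reverse, 88 × 0.90 = 79.2 (22 × 0.90 = 19.8 per arm). The loss at which 88 leaves exactly 80 is 1 − 80/88 = 9.1%. Taken alone, the Sample size section is coherent.

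**2. Do the two places describe the same step?**

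One way to reconcile them would be that 88 are recruited and 80 of these are randomised. The text does not allow this:

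- The 88 is given as 22 per group, and under Study design groups exist only after allocation, which follows the baseline assessment.
- The loss allowed for is loss to follow-up, which comes after randomisation.

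So 88 is a number allocated, and it conflicts with the abstract's 80.

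**3. Size of the conflict**

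| | Randomised | Left at 10% loss | Per arm | Against the end target of 80 |
|---|---|---|---|---|
| Sample size section | 88 | 88 × 0.90 = 79.2 | 19.8 | 0.8 short |
| Abstract | 80 | 80 × 0.90 = 72 | 18 | 8 short |

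The planned entry differs by 88 − 80 = 8 participants, or 2 per arm. If 80 were randomised, recruitment would be 80/80 = 100% of the abstract's figure and 80/88 = 91% of the Sample size section's figure.

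**4. The precedent for 20 per arm**

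A randomised sham-controlled trial has at least two arms. Twenty in each of two arms needs 2 × 20 = 40 participants. With 32, the average is 32 / 2 = 16 per arm, and less with more arms. No split of 32 puts 20 in every arm, so the unknown allocation ratio does not matter.

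**The case against.** The strongest reply is that little depends on either inconsistency. The Sample size section is explicit, and the competing figure is one sentence in an abstract. No power calculation uses these numbers. The Data analysis section defines the intention-to-treat population as all patients with a baseline assessment, whichever number was planned. The article sets no numerical criterion for recruitment; its only thresholds are for acceptability (75%) and tolerability (an average rating of 4 or less). All of this stands. It limits the consequence but does not remove the contradiction: the abstract does not shorten the figure, it gives a different one for the same step.

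A reader might infer three stronger points that the document does not support:

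- **That 88 is an arithmetic error.** The loss rate is stated only as approximate, and 9.1% loss leaves exactly 80. Even at exactly 10% the shortfall is 0.8 of a participant. A total of 92 (23 per arm) arises only by rounding up within each arm at exactly 10%.
- **That the denominator of the retention rate changes from place to place.** Retention is calculated on those actually randomised, and nothing in the article divides by a planned 80 or 88.
- **That the basis for 20 per arm collapses.** Reference 31 is one of two examples. The article gives no size for reference 41, so that support is neither confirmed nor contradicted.

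**Conclusion.** The point holds as an internal inconsistency with two parts.

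First, the planned number randomised is 80 in the abstract and 88 in the Sample size section, and one of them is wrong. The difference is 8 participants. At 10% loss the abstract's figure leaves about 72 (18 per arm) against a stated end target of 80. The 72 assumes that loss is exactly 10% and equal across arms; the conflict itself needs no assumption. The Sample size section's reading is the likelier one, because it gives its steps and they reproduce, but the article does not settle which number was intended.

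Second, reference 31 cannot be a trial with 20 in each arm if it had 32 participants. This rests only on its having at least two arms, which its description as randomised and sham-controlled implies.

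The consequence is modest. What is affected is how recruitment against plan can be described and how well the arm size is supported. The analysis, the analysis population and the retention rate are untouched. It is worth correcting because a stated sample size should be right and the correction is free.

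**What to change.** State once, and use throughout, whether 80 is the number randomised or the number expected at T2.

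- If the Sample size section is right, change the abstract to 88 randomised (22 per arm), with about 79 to 80 expected at T2 after roughly 10% attrition.
- If 80 randomised was intended, change the Sample size section instead, and give the expected number at T2 as about 72 (18 per arm).

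In the same section, remove reference 31 as support for 20 per arm, or describe its size as the Introduction does.

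The cost is a few words in two places. No further participants, no change of design and no new recruitment threshold are needed. As recruitment has ended, the clarification can go into the report of results, where the article says protocol amendments will be described.

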### Randomization

The study will use a randomized controlled design, stratified by age, gender and BMI. Participants will be randomly allocated to a study group in a 1:1:1:1 ratio. Randomization will be completed using the Sealed Envelope Simple+ randomization service (https://www.sealedenvelope.com/). After completing the T2 assessment, participants in the waiting control arm will be offered ABMT.

### Blinding and protection against bias

For pragmatic reasons, single-blinding will be implemented for [ABMT + real tDCS] and [ABMT + sham tDCS] groups. As such, participants in tDCS treatment groups will be blinded to real/sham allocation, but the researcher who leads treatment and conducts assessments will be unblinded. A validated protocol for sham stimulation will be used to deliver sham treatment; in the sham condition, tDCS electrodes will be properly mounted over the right and left dlPFC, and a 2mA current will be applied for 60 s at the beginning and end of each session. During the first and final 60 s of each session, no ABMT will be completed. Therefore, participants who receive sham will perceive typical sensations of tDCS (e.g., tingling), but will be unaffected by the stimulation. To assess if blinding was successful, participants will be asked to guess which condition they believe they have received and indicate how certain they feel about this. Once T2 and, where relevant the optional semi-structured interview about the treatment experience, are complete, participants will be unblinded. Those who receive sham treatment will not be offered any additional treatment. Blinding will not be implemented for ABMT only and waiting conditions.

The single-blind study design increases risk for experimenter bias. To protect against bias, self-report questionnaires (as opposed to interviews) will be used to assess clinical outcomes, including episodes of binge eating. All outcome measures will be collected online using either Qualtrics^XM^ for questionnaire measures, or Gorilla^TM^ or Inquisit Millisecond for neurocognitive task measures. As such, the experimenter will have no influence on participant responding or task performance. Semi-structured interviews about the treatment experience will be conducted before participants are unblinded and by independent investigators who are naïve to real/sham allocation.

### Intervention

Participants will complete 10 sessions of tele-supervised treatment over 2–3 weeks (i.e., week daily sessions until 10 sessions have been completed). Sessions will involve either concurrent ABMT and real/sham tDCS, or ABMT only. Participants in the waiting control arm will receive ABMT after completion of the T2 assessment.

#### Attention bias modification training

ABMT aims to train participants to “look toward” low-calorie food and “look away” from high-calorie food using a modified version of the anti-saccade task by Werthmann et al. (43). Training is completed on a personal laptop or desktop computer and lasts 10–15 min with breaks. Participants completing concurrent treatment (i.e., ABMT + real/sham tDCS) will begin ABMT 5 min after starting the stimulation. They will also be instructed to rest while waiting to begin and after completing the training.

##### ABMT paradigm

The modified task consists of 360 trials. Of these, 180 require participants to look toward low calorie foods, and 180 trials require participants to look away from high calorie foods. At the beginning of each trial, a black fixation point appears for 100 ms, followed by a red or blue fixation point (500 ms). A blue point indicates that a pro-saccadic eye movement is required (i.e., look toward the food picture which appears after the fixation point), whereas a red point requires an anti-saccadic eye movement (i.e., direct the gaze away from the food picture which appears after the fixation point). Low-calorie cues are always preceded by a blue dot and high calorie food cues are always preceded by a red dot. A blank screen is inserted for 200 ms between the fixation point and the stimulus presentation. The pictorial stimulus (a high- or low-calorie food picture) then appears on either the left or the right side of the screen for 500 ms. Inter-trial interval is 1,300 ms. Trials will be presented in a random order across three blocks, each including 120 trials. See Figure 1 for an example of a pro-saccade and anti-saccade stimulus presentation.

**Figure 1 F1:**
[figure not shown]
ABMT stimulus presentation. Left = pro-saccade stimulus presentation (i,e., participant is to look toward the food image presented). Right = anti-saccade stimulus presentation (i,e., participant is to move their gaze away from the stimulus).

##### Stimuli

Pictorial stimuli are 30 low calorie food and 30 high calorie food pictures, which are visually matched for brightness, color, and complexity, taken from Werthmann et al. (43). Each image is presented twice in each block, once on the left side of the screen and once on the right side of the screen (in a counterbalanced order), resulting in a total of 360 training trials (30 food stimuli + 30 non-food stimuli × 2 positions × 3 blocks).

##### Response and feedback

In addition to directing their gaze toward or away from the stimulus presented, participants will be instructed to press the arrow key which corresponds with the direction of their gaze. Response latencies will be recorded to monitor accuracy and provide participants with feedback. For each block, the number correct responses will be summed up and presented as percentage score of correct performance to the participant.

#### Self-administered transcranial direct current stimulation

Participant administered tDCS will be delivered using the Newronika HDC system (Figure 2). The Newronika system consists of an easy to use, lay friendly stimulator, a programming device used by the researcher to securely set stimulation parameters, and a customisable MindCap electrode placement system which ensures simple, safe, and reliable placement of the anode and cathode over the right and left dlPFC. Stimulation will be delivered at a constant current of 2 mA (with a 30 second fade in/fade out) for 20 min. This tDCS montage has been used in studies of food craving, bulimia nervosa, and BED (28, 32, 41, 44). As with real tDCS, sham stimulation will run for 20 min however, participants will not receive active stimulation for the full 20-min period. Instead, sham participants will receive 60 s of stimulation at the start (“ramping up”) and the end (“ramping down”) of the stimulation period.

**Figure 2 F2:**
[figure not shown]
Equipment for TDCS self-administration.

#### Rationale for session number and frequency

Although consensus around the optimal number of ABMT sessions is lacking, a review of meta-analyses of CBM concluded that the number of sessions appears to moderate outcomes, with higher session numbers being associated with greater change in cognitive bias (18). In line with this, Beard, Sawyer et al. (45) found that as session number increased, so did the potency of the effect of CBM on symptoms in depression, anxiety, and addiction disorders. However, this effect appeared to stabilize after 10 sessions. Therefore, 10 sessions may be the optimal dose for ABMT.

With regards to tDCS, although there is a similar lack of consensus about the optimal treatment parameters, it is broadly accepted that multiple sessions are needed to achieve lasting therapeutic effects (27, 44). The vast majority of multisession studies in psychiatric disorders have applied 10-sessions of tDCS once daily over 2–3 weeks (27). Thus, the choice of 10 sessions is also supported by the literature on tDCS use in psychiatric disorders.

#### Safety procedures

Published guidance for ensuring participant safety during self-administration of tDCS will be adhered to Knotkova et al. (46). This guidance is as follows: First, training and supervision should be provided to those self-administering tDCS. In TANDEM, all participants will be trained in safe tDCS self-administration, and all treatment sessions will be supervised *via* video-call. Second, the tDCS equipment used must be intended for home use by the lay community. We will use the Newronika HDC stimulator and MindCap electrode placement system which is CE marked for supervised home use in the UK and Europe. This equipment is pre-programmed by the researcher, simple to use, and includes features which prevent misuse (e.g., the researcher can set a minimum time between treatment sessions, and/or set a maximum number of sessions before re-calibration by the researcher). Third, care must be given to the participant's capacity for self-administration. Prior to beginning treatment, the TANDEM researcher will assess each participant's ability to self-administer tDCS safely. Where necessary, additional training will be provided. Participants who cannot safely self-administer tDCS after training will be withdrawn from the study, and the reason for their withdrawal will be reported. Fourth, tDCS tolerance and adverse events must be assessed at each session. Consistently, process outcomes will monitor tDCS tolerance and adverse events at each treatment session (see “Outcome Assessment” for more details), In addition, during or near to the final (T2) assessment, tDCS tolerance and adverse events will be assessed in an optional semi-structured interview about the treatment experience.

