## Study aims

The primary aim of the TANDEM trial is to assess the feasibility of using 10 sessions of concurrent food-specific ABMT (henceforth, ABMT) and self-administered right-dlPFC anodal tDCS as a treatment for BED. This intervention will be compared to training in combination with sham stimulation, stand-alone training, and a “no treatment” waiting control condition. In doing so, we aim to acquire key information to inform the design of a large-scale RCT.

Specifically, we aim to:
estimate the rate ratio for the proposed primary outcome, change in the number of monthly episodes of binge eating from baseline to follow up. This will inform the sample size calculation for a large-scale RCT.explore the feasibility of conducting a large-scale RCT of at-home self-administered concurrent tDCS and ABMT in adults with BED by assessing recruitment, attendance, and retention rates;assess acceptability by examining participant ratings of treatment acceptability and tolerance, and by evaluating feedback provided during semi-structured interviews;determine the best instruments for measuring primary and secondary outcomes in a full trial by examining the quality, completeness, and variability in the data.

The primary clinical endpoint will be the change in monthly episodes of binge eating from baseline to follow-up. Secondary aims will focus on evaluating changes in overall ED pathology and general psychopathology, changes in attention bias toward high-calorie foods, and changes in executive functioning from baseline to 6-weeks post treatment completion.

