**Figure 3 F3:**
[figure not shown]
TANDEM participant timeline.

Informed consent will be provided *via* an online consent form (Qualtrics^XM^). Once completed, potential participants will be screened over the phone for inclusion in the study. At screening, BED diagnosis is confirmed using a standardized interview [Eating Disorders Diagnostic Screen; (47)]. Physical and psychiatric comorbidities, current medications, and tDCS safety are assessed using a general health questionnaire developed for the purpose of screening. Eligible participants then complete the baseline (T0) assessment. After baseline assessment, participants are randomized to one of four groups: (1) ABMT + real tDCS, (2) ABMT + sham tDCS, (3) ABMT only, or (4) wait-list control group. Intervention groups will then complete 10 sessions of treatment, up to 5 sessions/week, across 2–3 weeks. The waitlist control group will receive no experimental treatment during this time. All participants will complete the post-treatment assessment (T1) after the 10^th^ (final) session of treatment or 2-weeks of waiting, and the follow-up assessment (T2) 6-weeks after completing treatment, or after 8-weeks of waiting. After completing the final (T2) follow-up, waiting control participants will receive ABMT.

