### Data analysis

The primary analysis will use the number of episodes of binge eating in a Poisson regression model with baseline adjustment. Descriptive statistics will be used to assess recruitment and retention rates, intervention adherence, and the quality and completeness of the data. In secondary analyses, a mixed model approach will be used to analyse the effect of treatment on primary (PO) and secondary outcomes (SOs), with baseline adjustment. To examine the whether the effect of treatment is different for different levels of overweight or obesity, BMI will be included in the model as an interaction effect. Effect sizes will be analyzed and reported for PO and SOs. For the Poisson regression, rate ratios will be reported. For binary outcomes, odds ratios will be reported. For quantitative outcomes, standardized differences will be reported. Primary parameters will be time vs. treatment interactions at both timepoints after baseline. *P*-values will be reported but for exploratory purposes only (i.e., they will not be interpreted to accept or reject the null hypothesis). The analyses will be done in the intent to treat population, which is defined by including all patients with baseline assessment. Outcome data already obtained for participants who discontinue or deviate from the intervention protocol will be kept and analyzed. Analyses will be conducted using RStudio (62).

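### Participants judged unable to self-administer tDCS leave the whole study, apparently after allocation, so their follow-up is lost and researcher-imposed exits are counted together with drop-out

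*Protocol article*

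**What the plan says.** All of this is in the protocol article.

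- **Safety procedures** states that "all participants will be trained in safe tDCS self-administration, and all treatment sessions will be supervised". It continues: "Prior to beginning treatment, the TANDEM researcher will assess each participant's ability to self-administer tDCS safely". Extra training is offered where needed, and then: "Participants who cannot safely self-administer tDCS after training will be withdrawn from the study, and the reason for their withdrawal will be reported".
- **Trial procedure** (text below Figure 3) gives the order as consent, telephone screening, T0, then allocation: "After baseline assessment, participants are randomized to one of four groups". Treatment follows. **Study design** gives the same order from T0 on. Neither lists device training or an ability check before allocation.
- **Inclusion criteria** opens with "Participants eligible for the trial must comply with all of the following criteria at randomization". Ability to self-administer is not in the list that follows.
- **Blinding and protection against bias** says that "the researcher who leads treatment and conducts assessments will be unblinded".
- **Data analysis** states: "The analyses will be done in the intent to treat population, which is defined by including all patients with baseline assessment". For participants who discontinue or deviate, it keeps the outcome data already obtained.
- **Study aims** includes exploring the feasibility of a large trial "by assessing recruitment, attendance, and retention rates". **Primary outcomes** adds that retention to 8 weeks will be reported and that the rate ratio will inform the size of that trial.

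**The concern.** Whether people can run the device at home is a central question for this feasibility trial. The rule answers it by ending study participation, not only stimulation. T1 and T2 consist of online questionnaires and computer tasks, so the safety purpose does not require their loss.

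Two results are at stake. First, a retention rate that combines exits imposed by the researcher with exits chosen by participants is a poor guide to the next trial, because the two have different causes and remedies. Second, if follow-up is missing for a selected subset of the tDCS arms, while the ABMT-only and wait-list arms have no equivalent selection, the contrast between them is no longer fully protected by randomisation. That rate ratio is meant to feed the next sample size calculation.

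**Working it through.** **Timing and arms.** The listed steps before allocation are consent, screening and T0. The tDCS safety item at screening belongs to a health questionnaire and is not a test of handling the device. Ability is not a criterion to be met at randomisation. The check is placed only before treatment. The natural reading is therefore a check after allocation. ABMT-only and wait-list participants use no device in the trial, so in practice the check would affect the two tDCS arms. This is an inference, since Safety procedures speaks of all participants and of each participant.

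**Data left.** Someone withdrawn before session 1 has T0 only. The analysis population keeps that person, but keeping data already obtained cannot supply a T2 count that was never collected.

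**The plan's own figure.** Sample size gives a target of 80, about 10% attrition, and 88 recruited (22 per arm). 80 × 1.10 = 88 reproduces it; 80 / 0.90 = 88.9, or 89, is within one. Expected completers: 88 × 0.90 = 79.2, or 22 × 0.90 = 19.8 per arm.

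**Illustration.** The documents give no number unable to self-administer. Assume *w* of 22 are withdrawn in each tDCS arm and 10% attrition applies to the rest.

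- Retention in a tDCS arm = (22 − *w*) × 0.90 / 22.
- Let *f* = *w*/22, and let *k* be the T2 binge rate that those withdrawn would have had, relative to the others in their arm. The arm's true mean is *m*[(1 − *f*) + *fk*] and the observed mean is *m*. So observed/true rate ratio against a non-tDCS arm = 1 / [(1 − *f*) + *fk*], before baseline adjustment.

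| *w* of 22 | Retention, tDCS arm | Retention, all 88 | Ratio, *k* = 0.67 | Ratio, *k* = 1.5 | Ratio, *k* = 2 |
|---|---|---|---|---|---|
| 0 | 19.8/22 = 90.0% | 79.2/88 = 90.0% | 1.000 | 1.000 | 1.000 |
| 2 | 18.0/22 = 81.8% | 75.6/88 = 85.9% | 1.031 | 0.957 | 0.917 |
| 4 | 16.2/22 = 73.6% | 72.0/88 = 81.8% | 1.064 | 0.917 | 0.846 |

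With *k* = 1 the ratio is 1.000 for every *w*.

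**Real versus sham.** With equal *w* and *k* in both arms the shift cancels: 1.000. With 2 withdrawn from real and 1 from sham, the shift is [(21 + *k*)/22] / [(20 + 2*k*)/22]: 22.5/23 = 0.978 for *k* = 1.5, and 23/24 = 0.958 for *k* = 2.

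**After the change.** If T1 and T2 are still sought and those stopped attend like the others, expected retention returns to 90% in every arm and the shift due to this rule disappears.

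**The case against.** Several points on the other side stand.

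- **Timing is not stated.** Safety procedures refers to all participants, and the timeline figure is not available here. If the check came before allocation, it would restrict enrolment and cause no bias between arms. A condensed article may also leave this detail to the full protocol. Even so, the sections that are present put no check before allocation.
- **It is not an exclusion from analysis.** A reader might infer that these participants are dropped from the intent-to-treat population. They are not, because that population includes everyone with a baseline assessment. The harm is missing follow-up.
- **The failure is not hidden.** The reason for withdrawal is to be reported, and Exclusion criteria also promises the number who withdraw, with reasons where provided. What is missing is a separation of the two kinds of exit within the retention rate.
- **Acceptability and discomfort ratings.** A reader might infer that these are lost too. Someone withdrawn before session 1 has no session to rate, and the 75% acceptability criterion covers only those who receive the real combined treatment.
- **The size is assumed.** Neither *w* nor *k* has a source in the documents. A simple device, extra training and video supervision suggest small numbers. The 10% attrition may already include such exits; total retention would then not fall below plan, but its make-up would still be unclear. Baseline adjustment may absorb part of any shift.
- **Unblinded judgement.** A reader might infer that real versus sham is biased. Both arms handle the same device, and nothing shows that withdrawals would differ. The documents support only the possibility.

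**Conclusion.** The point holds in a limited form. As written, the rule ends follow-up for people whose follow-up could be collected remotely, and on the natural reading it does so after allocation and in the tDCS arms. It mixes imposed exits with participants' own drop-out in a feasibility outcome, and it can bias contrasts with the ABMT-only and wait-list arms. Real versus sham is affected only if the number or type of people withdrawn differs between those two arms.

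Under the stated assumptions, 2 to 4 withdrawn of 22 lowers retention in a tDCS arm from 90% to between 82% and 74%. A true rate ratio of 1.00 would read between 0.96 and 0.85 if those withdrawn would have had 1.5 to 2 times the others' rate, and between 1.03 and 1.06 if they would have had 0.67 times. Actual size and direction are unknown. The conclusion rests on the inferred timing and on reading withdrawal from the study as the end of T1 and T2 collection.

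**What to change.** The safety decision, and any decision on continuing treatment, stays with the sponsor. The changes concern follow-up and reporting:

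1. State that stopping because of inability to self-administer does not end follow-up: T1 and T2 are still sought at the scheduled times and analysed in the allocated arm.
2. Report the number unable to self-administer in each tDCS arm, over all allocated to that arm, as a feasibility outcome separate from participant-initiated drop-out.
3. Reconcile Safety procedures, Trial procedure and Data analysis on who is assessed and whether this is before or after randomisation. If before, place the check in the procedure and apply it to all four arms.

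The cost is a few sentences and up to two online assessments for each of a few participants, with no extra staff. Trial progress says that recruitment ended in February 2022 and that data collection was to finish by June 2022. If it has finished, the first change may come too late, but the separate reporting and the clarification of timing still apply.
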